#### Strategies to improve adherence to interventions {11c}

Subjects will be instructed to complete a drug diary during the treatment period. The diary will be reviewed in all follow-up interactions with the subject. The subject will be asked to return any unused medication at the end of the treatment period to monitor compliance with the study protocol.

#### Relevant concomitant care permitted or prohibited during the trial {11d}

Phosphodiesterase type 5 (PDE5) inhibitors are excluded within the first 3 months of enrollment. Subjects will be screened prior to enrollment to determine previous use of PDE5 inhibitors. Subjects who have taken PDE5 inhibitors more than once a week, because they cannot achieve an erection sufficient for intercourse without the medication, will not be excluded from the study but will be required to discontinue their use for 3 months while enrolled in the study.

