#### Criteria for discontinuing or modifying allocated interventions {11b}

Subjects will be withdrawn from the study for the following:If the subject is unable or unwilling to take the study drug.Subjects planned for a NSRP but who did not receive a nerve-sparing procedure intraoperatively.Subjects who have experienced a seizure while taking the study medication.Subjects who take ED treatments within the 3-month period after surgery.Any subject with an eGFR less than 60 mL/min/1.73 m^2^ while on the study, if clinically indicated, will have a repeat serum BUN and creatinine within 2–3 days, and if eGFR is still less than 60 mL/min/1.73 m^2^, they will be promptly withdrawn from the study.In subjects who incidentally demonstrate a decrease in eGFR > 30 mL/min on study, but still maintain an eGFR ≥ 60 mL/min, we will obtain repeat BUN and creatinine within 2–3 days, and if eGFR based on repeat labs is < 60 mL/min, they will be promptly withdrawn from the study.Subjects with final surgical pathology showing pT3 disease, positive nodes, or positive surgical margins who require adjuvant treatment (such as androgen deprivation therapy or radiation) as adjuvant treatments can worsen ED and UI after NSRP.The Data Safety Monitoring Committee (DSMC) and/or principal investigator may withdraw any subject at increased risk using the best medical opinion based on reported AEs/SAEs.

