### Outcomes {12}

#### Primary outcome

The primary outcome is return to baseline confidence in the ability to achieve and maintain erection as measured by item 1 of the Abridged International Index of Erectile Function (IIEF-5) by 12 weeks after surgery.

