## Research visit 1 (pre-op)

At research visit 1, informed consent will be obtained, eligibility confirmed, medical history and concomitant medications collected, and we will obtain a urinalysis, CBC, and BMP, if not done as pre-operative standard of care.

In addition, two questionnaires will be administered pre-operatively as part of the standard of care practice. The Michigan Incontinence Symptom Index (M-ISI) and the Abridged International Index of Erectile Function (IIEF-5) are standardized measures of the consequences of radical retro-pubic prostatectomy and will be used to track this debilitating set of consequences. Subjects will also complete a 3rd questionnaire, the Attempted Sexual Intercourse and Erectile Aids questionnaire, as a part of this study.

## Post-op day 1

Subjects will have a visit with study personnel on the first day after their surgical procedure.

Greater than 90% of those who undergo robot-assisted RRP are discharged on post-operative day #1. A physical exam and vital signs will be obtained as part of the standard of care. Subjects will begin treatment (either study drug or placebo) while in the hospital, prior to discharge. This will allow dosing instructions to be clearly reviewed with subjects and the first dose administered while in the care of a facility. Initial dose time and date will be logged in the subject drug diary with the subject and accompanying family members to help emphasize the adherence to the protocol during the 2-month treatment period. Dosing instructions, study drug compliance, and completion of the subject drug diary will be reviewed in all follow-up interactions with the subject. Subjects will be instructed to return bottle #1 at the week #4 visit.

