## Statistical methods

### Statistical methods for primary and secondary outcomes {20a}

#### Planned statistical analysis

The data analysis will be based on the principle of intention to treat.

(1) Descriptive statistics:

Descriptive statistics for all covariates and outcomes will be reported. For categorical variables, the frequency will be reported. Pearson’s chi-square test or Fisher’s exact test will be used to compare the difference between the two groups. For continuous variables, the mean, standard deviation, and median will be calculated. Two-sample *t*-test (for normally distributed data) or Wilcoxon rank test will be used to compare them in the two groups.

(2) Analysis of outcomes:

(2.1) Analysis of the primary outcome.Pearson’s chi-square test will be used to compare the rates of returning to the baseline ability by the end of the follow-up.Since this is a longitudinal study, we anticipate some patients will drop out during the follow-up. We assume that the dropout is monotone and random, which means that once they drop out, they will not come back to the study, and the dropout only depends on the information up to the point of dropout. We will model the probability of dropout by logistic regression. The weighted generalized estimation equation (GEE) (with logit link) will be used to study the treatment effects on the returning to the baseline ability at each visit after adjusting the effects of some baseline demographic and clinical factors [14, 15].

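### Regular PDE5-inhibitor users may be asked to match a drug-assisted baseline off drug, and the primary chi-square adjusts for neither prior use nor the baseline item 1 score

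*Protocol article*

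**What the plan says.** All references are to the protocol article.

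- **Concomitant care {11d}.** Men taking PDE5 inhibitors more often than weekly "because they cannot achieve an erection sufficient for intercourse without the medication, will not be excluded from the study". The section adds that they have to stop for 3 months. Previous use is determined at screening.
- **Eligibility criteria {10}.** Entry needs an IIEF-5 of at least 17 at screening. Nothing says whether that score is with or without medication.
- **Research visit 1 (pre-op).** Consent is taken and eligibility confirmed, and "two questionnaires will be administered pre-operatively as part of the standard of care practice"; the IIEF-5 is one of the two. No drug-free condition is attached.
- **Discontinuation criteria {11b}.** "Subjects who take ED treatments within the 3-month period after surgery" are withdrawn, so the 12-week score is meant to be drug-free.
- **Primary outcome.** This is "return to baseline confidence in the ability to achieve and maintain erection as measured by item 1" of the IIEF-5, by 12 weeks.
- **Planned statistical analysis, (2.1).** Pearson's chi-square is used to "compare the rates of returning to the baseline ability by the end of the follow-up". A weighted GEE with logit link is listed under the same heading, adjusted for baseline demographic and clinical factors that are not named.
- **Sample size {14}.** The calculation rests on the chi-square, with return rates of 70% and 30%.
- **Sequence generation {16a}.** Randomisation is in blocks. No stratification by prior use or baseline score is described.

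**The concern.** A man who, as {11d} describes him, cannot manage intercourse without the drug but still scores 17 or more may well have answered for his function on the drug. If so, his target is a drug-assisted score and his 12-week result is drug-free. For him the endpoint mixes two things: recovery of the injured nerves, which the trial is about, and withdrawal of a medicine, which it is not.

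The protocol sees this hazard after surgery. The choice of comparator {6b} and the Discussion both restrict PDE5 inhibitors because uneven use would confound. It does not deal with the same hazard in the baseline.

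Men who are less likely to return whichever capsule they receive shrink the difference between arms. In a trial of 40 per arm they can also fall unevenly by chance. The test that carries the sample size uses neither prior use nor the baseline item 1 score, though both are known before surgery.

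**Working it through.** **1. The plan's own figure.** Inputs from Sample size {14}: 70% v 30%, 90% power, significance level 0.05 (taken as two-sided), 30% dropout.

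With unpooled variance, n = (1.960 + 1.282)² × (0.7×0.3 + 0.3×0.7) / 0.4² = 10.507 × 2.625 = 27.58, so 28 per arm. Then 28 / 0.70 = 40. Both stated figures reproduce.

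At 28 per arm the uncorrected Pearson test has 87.0% power by the pooled-variance formula and 86.1% by exact enumeration over all pairs of binomial counts. The 86.1% is the reference below.

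**2. Effect of men with a harder target.** Let f be their share and q their return rate in an arm. The arm's rate is (1 − f) × p + f × q, with p = 70% or 30%. The documents give neither f nor q, so both are assumptions. Two cases are shown: they never return (q = 0% in both arms), or their rates are halved (q = 35% and 15%). For example, f = 20% with q = 0 gives 0.8 × 70 = 56% and 0.8 × 30 = 24%.

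**3. Does stratifying help?** The same scenarios were simulated with a Mantel-Haenszel test stratified on prior use.

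| f | Return of prior users | Arm rates | Exact power, chi-square, 28 per arm | Power, stratified test |
|---|---|---|---|---|
| 0 | – | 70% v 30% | 86% | – |
| 10% | never | 63% v 27% | 78% | 83% |
| 20% | never | 56% v 24% | 69% | 78% |
| 30% | never | 49% v 21% | 61% | 72% |
| 10% | halved | 66.5% v 28.5% | 82% | 84% |
| 20% | halved | 63% v 27% | 78% | 80% |
| 30% | halved | 59.5% v 25.5% | 74% | 77% |

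Before rounding, the gain from stratifying runs from about 1.5 points (f = 10%, halved) to about 11 points (f = 30%, never). It does not restore the diluted effect: at f = 20% with no returns, the overall risk difference is 56 − 24 = 32 points instead of 40, whatever the test.

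**4. Type I error.** With no treatment effect and prior users never returning, the exact size of the chi-square at 28 per arm is 4.8% at f = 20% and at f = 30%, against 5.2% at a common rate of 30%. The stratified test stays near 5%. Nothing is inflated.

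**5. Chance imbalance.** With independent binomial counts, the probability that the arms differ by 4 or more prior users is 12%, 24% and 31% (f = 10%, 20%, 30%) at 28 per arm, and 19%, 33% and 39% at 40 per arm.

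**The case against.** The strongest reply has four parts.

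*The plan does adjust.* The weighted GEE stands under the primary-outcome heading and is covariate-adjusted. A reader might infer that the plan disregards baseline information altogether; it does not. Nor is the baseline score ignored, since it sets each man's target. Naming the covariates may be left to an analysis plan that is not shown. This stands. But the GEE is not the test that sizes the trial, and no choice of covariates tells us whether a baseline answer was drug-assisted.

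*The unadjusted chi-square is valid.* Allocation is randomised and step 4 shows no inflation. Chance imbalance affects any unstratified prognostic factor and is already within the test's error rate. This stands too: a reader might infer bias between arms or a false-positive problem, and neither follows. What remains is avoidable loss of power and precision.

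*The size is assumed.* A reader might infer that these men are almost certain not to return. The documents give no return rates for them, do not say that their answers were drug-assisted, and use an endpoint that is confidence on one item, not intercourse. So the never-return rows are an extreme, and the halved-rate rows belong beside them. The 70% and 30% are also stated for the enrolled population without exception. If they already include these men, nothing is lost against plan.

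*Adjustment does not cure dilution.* Correct. It recovers part of the power only.

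**Conclusion.** The point holds as one of endpoint definition and efficiency. The protocol article leaves open whether baseline is drug-free for men it describes as dependent on PDE5 inhibitors, then scores their return off drug. The test behind the sample size takes no account of prior use or of the baseline item 1 score.

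Over the assumed range (10% to 30% of men; no return or halved return; 28 evaluable per arm), chi-square power drops from 86% to between 82% and 61%. Stratifying on prior use recovers about 1.5 to 11 points. The loss against plan is nil if 70% and 30% already allow for such men. The gain from also adjusting for item 1 cannot be quantified, because no distribution of that score is given.

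A reader might conclude that the sample size is wrong on this account. It is not: 28 and 40 per arm follow from the stated inputs.

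**What to change.** 1. Record at baseline whether the IIEF-5 answers refer to function with or without PDE5 inhibitors, and state what return to baseline means for prior regular users. For men already enrolled, prior use should be available from screening.
2. Make the primary test covariate-adjusted for prior regular PDE5-inhibitor use (yes/no) and baseline item 1 score. Use a method that tolerates empty cells: a Mantel-Haenszel stratified test with its risk difference, or Firth-penalised logistic regression with a standardized risk difference. Plain logistic regression is unsafe here, because if no prior user returns the coefficient for prior use has no finite estimate.
3. Name the same two covariates in the weighted GEE.
4. Keep Pearson's chi-square as the supportive unadjusted test, and add a sensitivity analysis without prior regular users.

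The cost is one extra baseline item and a slightly more complex primary analysis. The analysis change should be fixed before unblinding, and it alters no participant's treatment.

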#### Provisions for post-trial care {30}

The subject and/or the subject’s insurance company will be responsible for all standard of care costs associated with post-operative radical retro-pubic prostatectomy (PDE5 inhibitors, vacuum pumps, urethral suppositories, injection therapy). Subjects will be encouraged to contact their insurance company for insurance coverage costs prior to the standard of care treatments offered in this study.

No compensation is planned for trial-related injury.

### Outcomes {12}

#### Primary outcome

The primary outcome is return to baseline confidence in the ability to achieve and maintain erection as measured by item 1 of the Abridged International Index of Erectile Function (IIEF-5) by 12 weeks after surgery.

#### Secondary outcomes

The following are the secondary outcomes:Return to baseline erectile function as measured by the IIEF-5A more rapid recovery (time frame) of subject-reported erectile function measured by the Abridged International Index of Erectile Function (IIEF-5)Improved recovery of baseline subject reported continence using the Michigan Incontinence Symptom Index (M-ISI) in the intervention groupDecreased use of medications and devices for erectile dysfunction measured by the Attempted Sexual Intercourse and Use of Erectile Aids questionnaire

#### Participant timeline {13}

[figure not shown]

## Research visit 1 (pre-op)

At research visit 1, informed consent will be obtained, eligibility confirmed, medical history and concomitant medications collected, and we will obtain a urinalysis, CBC, and BMP, if not done as pre-operative standard of care.

In addition, two questionnaires will be administered pre-operatively as part of the standard of care practice. The Michigan Incontinence Symptom Index (M-ISI) and the Abridged International Index of Erectile Function (IIEF-5) are standardized measures of the consequences of radical retro-pubic prostatectomy and will be used to track this debilitating set of consequences. Subjects will also complete a 3rd questionnaire, the Attempted Sexual Intercourse and Erectile Aids questionnaire, as a part of this study.

## Post-op day 1

Subjects will have a visit with study personnel on the first day after their surgical procedure.

Greater than 90% of those who undergo robot-assisted RRP are discharged on post-operative day #1. A physical exam and vital signs will be obtained as part of the standard of care. Subjects will begin treatment (either study drug or placebo) while in the hospital, prior to discharge. This will allow dosing instructions to be clearly reviewed with subjects and the first dose administered while in the care of a facility. Initial dose time and date will be logged in the subject drug diary with the subject and accompanying family members to help emphasize the adherence to the protocol during the 2-month treatment period. Dosing instructions, study drug compliance, and completion of the subject drug diary will be reviewed in all follow-up interactions with the subject. Subjects will be instructed to return bottle #1 at the week #4 visit.

## Post-op days 2–5

For the first 5 days after surgery, subjects will be contacted by study personnel in person (post-op day #1) and by telephone (post-op days #2–5) to monitor for potential side effects. Any adverse events will be documented. In addition, the study drug and diary will be reviewed to ensure accuracy and completion, and any questions the subjects may have about the study will be answered.

## Post-op days 7–10

On post-op days 7–10 (± 3 days to accommodate provider/subject schedules), subjects will have a standard-of-care clinic visit which will include a brief physical exam (surgical site, abdominal and genital exam, and review of systems) and have vital signs checked. As part of the standard of care, subjects will be encouraged to perform Kegel exercises at this visit.

## Post-op week 3

At post-op week 3, any adverse events will be checked, and the study drug and diary will be reviewed via telephone using the Telephone Log and Script Form. Subjects will complete the three questionnaires (research procedures).

## Post-op weeks 4, 6, and 8

Subjects will have a research visit with study personnel at weeks 4 and 8 (± 3 days), which will include administration of the three questionnaires, study drug and diary compliance, and a check of any adverse events. At post-op week 4, subjects will return bottle #1 of the study drug, and bottle #2 will be dispensed. They will be instructed to return their completed drug diary at each study visit and any unused medication at the end of the treatment period (week 8). As an internal control, subjects will be asked to complete an additional questionnaire at week 8 to assess whether they think they received the active drug or placebo. On week 6, subjects will receive a call from study personnel to assess the adverse events and instruct subjects to complete their questionnaires.

## Post-op week 10 to month 6

Completion of the three questionnaires will continue every other week from post-op week 10 to month 6 (research procedure), and every effort will be made to collect them. Adverse events will be captured and monitored by the study staff.

## Post-op months 3, 6, 9, and 12 visits

As part of the post-operative standard of care, subjects will be seen at 3 months, 6 months, 9 months, and 12 months (± 14 days). Subjects will be offered treatment for erectile dysfunction starting at 3 months post-op and for the duration of the study. Treatment options will be guided by the results from the IIEF-5 questionnaire and algorithm for erectile dysfunction and include oral agents (PDE5 inhibitors) or any type of non-surgical erectile dysfunction treatments (penile pump, urethral suppositories, intracavernosal injections). At these visits, we will obtain the three questionnaires, physical exam, and vital signs (as part of the standard of care) and also query for adverse events. PDE5 inhibitors include drugs such as Viagra (sildenafil), Cialis (tadalafil), and Levitra (vardenafil) will be the drugs prescribed for post-operative erectile dysfunction as part of the standard of care. The surgeon and/or a member of the study team will be the prescriber of these medications 3 months after surgery. We will review PDE5 use with post-operative questionnaires.

Subject medical records will be reviewed to collect basic demographic information, as well as information about the subject’s medical and surgical history, diagnosis, surgery, clinical lab and pathology results, imaging results, and clinical outcomes.

## Sample size {14}

The primary outcome is return to baseline ability to achieve and maintain erection as measured by Item of the Abridged International Index of Erectile Function (IIEF-5) by 12 weeks after surgery. Suppose at the conclusion of the follow-up period, the rates of returning to the baseline ability in the treatment and control groups are 70% and 30%, respectively. Pearson’s chi-square test indicates that a sample size of 56 (with 28 individuals in each group) achieves 90% power to detect the intended difference of 40% (at a significance level of 0.05). Accounting for an estimated dropout rate of 30%, we plan to recruit 40 subjects in each group.

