#### Intervention description {11a}

Subjects will be randomized equally into one of two groups. Both the subject and investigators will be blinded to group assignment.The treatment group (40 subjects) will receive the study drug daily, in two oral doses, taken at least 12 h apart (approximately 8:00 am; 8:00 pm), starting on the day after surgery with the approximately 8:00 am dose. The treatment group will continue at this same dose and daily dosing regimen for 2 months (60 days).The placebo group (40 subjects) will receive a placebo daily, in two oral doses, taken at least 12 h apart (approximately 8:00 am; 8:00 pm), starting on the day after surgery with the approximately 8:00 am dose. The placebo group will continue at this same dose and daily dosing regimen for 2 months (60 days).

The following are the dosing instructions:Dosing schedule = 1 capsule in the morning and another capsule 12 h later (approximately 8:00 am; 8:00 pm).Dosing to begin the day after surgery with the 8:00 am dose.Subjects will not take more than two capsules in a 24-h period.Subjects will take the capsules whole. They will not break, crush, chew, or dissolve capsules before swallowing. The subjects will be told that the medication is released slowly over time, and if the tablet is broken, the medicine may be released too fast which can raise the chance of having a seizure.The study drug can be taken with or without food.If a dose is missed, they should not make up the missed dose; however, subjects may take the dose within 1 h of the scheduled time. They will be told not to take two doses at the same time but to take the next dose at the regular scheduled time.If the subject is unable to take the study medication due to surgical complications (such as ileus), the doses will be skipped and the subject will resume the study medication once able to take other medications by mouth. The subject will not make up the missed doses.Subjects will be reminded not to take the study drug together with other aminopyridine medications, including compounded 4AP (sometimes called 4-aminopyridine or fampridine).

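### With 28 evaluable men per group, a two-sided Pearson chi-square test has about 87% power for 70% v 30%, not the stated 90%, which needs 31 per group

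*Protocol article*

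**What the plan says.** The Sample size section assumes that "the rates of returning to the baseline ability in the treatment and control groups are 70% and 30%, respectively". It then reports that, for Pearson's chi-square, "a sample size of 56 (with 28 individuals in each group) achieves 90% power to detect the intended difference of 40" percentage points, "at a significance level of 0.05". The inflation follows: "Accounting for an estimated dropout rate of 30%, we plan to recruit 40 subjects in each group".

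The statistical methods section (Planned statistical analysis) names the same test for the primary outcome: Pearson's "chi-square test will be used to compare the rates of returning to the baseline ability by the end of the follow-up". Allocation is 1:1 (Intervention description: "Subjects will be randomized equally into one of two groups").

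The article does not say whether the 5% level is one- or two-sided, which variance formula lies behind the 28, or what software was used.

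**The concern.** The article supplies every input needed to check the figure except sidedness: both rates, the significance level, the test, the group size and the power. It ties the power to the same test that will be used for the primary outcome. Pearson's statistic takes its variance from the pooled proportion under the null hypothesis. With rates as far apart as 70% and 30%, the pooled variance is clearly larger than the unpooled one, so the two formulas give different sample sizes.

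At stake is a reported design property. If 28 men per group are evaluable, the chance of missing a true 40-point difference is about 13% to 14%, where the article implies 10%. The recruitment target was built from the 28 with no further margin, so nothing else in the calculation absorbs the difference.

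**Working it through.** **Inputs.** p1 = 0.70, p2 = 0.30, difference d = 0.40, alpha = 0.05, n = 28 per group, stated power 90%, dropout 30%, 40 recruited per group (all from the Sample size section). Two-sided testing is assumed, because Pearson's statistic does not distinguish direction. Hence z(0.975) = 1.960 and z(0.90) = 1.2816.

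**1. Reproducing the plan's figure.** The unpooled-variance formula gives

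n = [p1(1−p1) + p2(1−p2)] × (1.960 + 1.2816)² / d² = 0.42 × 10.507 / 0.16 = 27.58, rounded up to 28.

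Its approximate power at 28 is Φ(0.4/√(0.42/28) − 1.960) = Φ(1.306) = 90.4%. This matches the article. That the authors used this formula is inferred from the match; the article does not say so.

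**2. The formula that belongs to the named test.** The pooled proportion is 0.5, so the null term is √(2 × 0.5 × 0.5) = √0.5.

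Power at 28 = Φ[(0.4 × √28 − 1.960 × √0.5) / √0.42] = Φ[(2.1166 − 1.3859) / 0.6481] = Φ(1.13) = 87.0%.

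n for 90% = (1.960 × √0.5 + 1.2816 × √0.42)² / 0.16 = (1.3859 + 0.8305)² / 0.16 = 30.70, rounded up to 31.

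**3. Exact check.** The probabilities of all pairs of binomial counts (70% and 30%) for which the uncorrected chi-square is significant at two-sided 0.05 were summed. The last column is the loss from 40 per group that leaves n.

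| n per group | Pooled approximation | Exact, Pearson | Dropout from 40 |
|---|---|---|---|
| 28 | 87.0% | 86.1% | 30% |
| 30 | 89.3% | 89.6% | 25% |
| 31 | 90.3% | 91.1% | 22.5% |
| 32 | 91.2% | 92.4% | 20% |
| 36 | 94.1% | 93.4% | 10% |
| 40 | 96.1% | 96.4% | 0% |

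Exact power stays above 90% at every n from 31 to 40.

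**4. Other readings of the 28.** None of these yields 28 as the size for 90% power:
- arcsine: 31.02, so 32 (86.9% at 28)
- non-central chi-square with effect size 0.4: 33 (84.9% at 28)
- continuity-corrected: 36
- one-sided 0.05, pooled: 25 (92.9% at 28)

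Actually testing with the unpooled statistic would not restore 90% either: its exact power at 28 is 87.4%.

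**5. Inflation.** 28 / (1 − 0.30) = 40, as stated, so this step is correct. Starting from 31 it would be 31 / 0.70 = 44.3, so 45. With 40 recruited, 31 remain if the loss is no more than 1 − 31/40 = 22.5%.

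**The case against.** The best defence is that 28 per group is no slip of arithmetic. It follows from a standard sample-size formula for two proportions, and the dropout inflation is done properly. A reader might infer from the mismatch that the calculation was botched. The document does not support that: the figure reproduces under a recognised formula, and the fault lies in attributing it to Pearson's test. This tempers the criticism but does not remove it, since the planned analysis is Pearson's test and the exact power is about 86% to 87% whichever of the two variances the test uses.

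Second, the shortfall is conditional. A reader might infer that the trial as a whole has only 86% to 87% power. That holds only if the full 30% are lost and 28 per group remain. With 40 recruited, power is at least 90% for losses up to 22.5% in each group and about 96% with none. At 30 evaluable per group it is already 89.6% exact, so the practical gap is two to three men per group. This part of the objection stands in full.

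Third, a reader might go further and count dropouts as not having recovered, which would lower power well below 87%. No section states such a rule. The sample size calculation treats dropouts as not evaluable, and the statistical methods and missing-data sections assume data missing at random and plan a weighted GEE with modelled dropout. No power figure should be built on a rule that the article does not contain.

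Fourth, sidedness is unstated, and under a one-sided 0.05 test 28 per group would exceed 90%. Such a test would have needed only 25 per group, however, so it does not explain the choice of 28, and Pearson's test is ordinarily read as two-sided.

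**Conclusion.** Wrong as written, and minor. For the named test the stated 90% should be about 87% (pooled approximation) or 86.1% (exact) at 28 evaluable men per group, a gap of 3 to 4 points. Put the other way, 90% needs 31 evaluable per group, 3 more than stated.

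The conclusion rests on a two-sided 5% level, the uncorrected Pearson statistic, the article's own assumed rates of 70% and 30%, and the full 30% dropout. The mismatch affects how the design is described. It does not bias the treatment comparison or alter its type I error, and it gives no ground for calling the trial underpowered at the planned 40 per group.

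**What to change.** Replace the power sentence in the Sample size section with, for example: *28 evaluable subjects per group give about 87% power (two-sided Pearson chi-square, alpha 0.05) for 70% v 30%.* Keep 40 per group and the 30% dropout allowance as they are.

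This costs one sentence and a slightly less favourable stated power. No extra patients are needed and the analysis does not change. The Trial status section puts the start of enrolment in December 2019 and the expected end of recruitment in mid-2023, which also favours correcting the wording over enlarging the trial.
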